### Plans to promote participant retention and complete follow-up {18b}

The patients will receive extensive information about the study set-up and requirements during the recruitment. The importance of completion of the follow-up will be stressed. Patients are allowed to stop at any time during the study and are not obliged to give a reason to discontinue. If possible, the patient will be asked to complete the online survey at 9 months after inclusion. Questionnaires are completed using an online survey, and therefore patients can do this at any convenient moment. All patients are reminded throughout the study to fill out the questionnaires during study visits. Throughout the follow-up period, the researchers will check responses and if necessary contact patients for completion of their follow-up.

### Data management {19}

Patient data will be collected with a GCP compliant eCRF (Castor EDC) [26]. Questionnaires will be answered online and output will be stored in SPSS. Back-ups in the study folder on the protected research server will be made regularly(once per 3 months). Informed consent and end-of-trial dates will be recorded in the electronic patient dossier and signed paper forms will be stored within our hospital in a locked room. (S)AEs will be recorded in the eCRF. To be able to reproduce study results and to help future users to understand and reuse data, all changes made to the raw data and all steps taken in the analysis will be documented in the eCRF and IBM SPSS (version 15.0.0.2, Chicago, IL). Source data will remain available in electronic patient record and OnlinePROMS. All research data, including patient material, will be archived for 30 years after the study has ended according to the guidelines for Advanced Therapy Medicinal Products (ATMPs).

### Confidentiality {27}

Research data will be stored using a study identification code for each participant. The key to the identification code list will only be available to the research team during the study and will be documented and safeguarded by the principal investigator according to research guidelines after completion of the study. No patient identification details will be reported in publications.

### Plans for collection, laboratory evaluation, and storage of biological specimens for genetic or molecular analysis in this trial/future use {33}

In the case of leftover material, this will be stored within the Cell Therapy Facility according to the ATMP legislation.

## Statistical methods

### Statistical methods for primary and secondary outcomes {20a}

Data will be analyzed using IBM SPSS (version 15.0.0.2, Chicago, IL). Data from the primary objective (KOOS, EQ-5D-5L) will be presented as continuous variables. To compare between the two treatment groups, a mixed model analysis will be performed, with treatment group and assessment date of the PROMs (e.g., baseline, 3 months, 6 months) as fixed factors. Differences will be considered statistically significant for the fixed effect of treatment groups if *p* < 0.05 [30]. The 95% confidence interval of the fixed effect size will be used to assess whether treatment difference reaches the minimally clinical important difference.

T1rho-scores will be calculated from the biochemical MRI scans; differences in T1rho-scores will be compared between the time points *t* = 0 (at inclusion before IMPACT or nonsurgical treatment) and *t* = 6 and 18 months after inclusion or surgery. Differences will be compared using Student’s *t* test. The differences in T1rho-score will be tested for normality using Q–Q plots. *P* values less than 0.05 will be considered significant. We will calculate the ICERs of IMPACT vs. nonsurgical treatment and vs. delayed surgical treatment in terms of cost/QALY over a 5-year time horizon. The effect of uncertainty in input parameters on the ICERs will be calculated by means of one-way sensitivity analysis as well as probabilistic sensitivity analyses using Monte Carlo simulation.

All (S)AE(I)s will be summarized and recorded including the nature, date and time of onset, date of resolution, determination of seriousness, severity, action taken, outcome, and possible causality to study treatment. SAE data will be presented in a descriptive manner.

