### Sample size {14}

The sample size was calculated for the primary objective (treatment effect up to 9 months postoperatively) based on the Hotelling-Lawley trace [24, 25]. Based on a standard deviation of 15 [23], correlation of the repeated measures of 0.7 (data from our phase I trial [21]), and with a power of 0.8 and alpha of 0.05, a minimum of 44 patients should be included to detect a minimal clinical relevant treatment effect of 10 for KOOS [23]. To account for potential loss to follow-up, and uncertainties in the correlation pattern and standard deviation for nonsurgical treatment, this was rounded up to 60 patients in total.

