## Assignment of interventions: allocation

### Sequence generation {16a}

Patients will be randomized into variable block sizes of two and four, stratified by defect size (< 4 or ≥ 4 cm^2^), using Castor EDC [26].

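### The listed primary model omits the defect-size stratum used in randomisation, so the standard error of the group effect is overstated to the extent that defect size predicts KOOS

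*Protocol article*

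**What the plan says.** Under Sequence generation {16a}, the protocol article states: "Patients will be randomized into variable block sizes of two and four, stratified by defect size", with classes of < 4 and ≥ 4 cm². Defect size is the only stratification factor.

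Under Statistical methods for primary and secondary outcomes {20a}, the between-arm comparison is specified as follows: "a mixed model analysis will be performed, with treatment group and assessment date of the PROMs" as fixed factors. The examples in brackets there (baseline, 3 months, 6 months) illustrate the assessment dates, not the list of factors. Neither that section nor the sections on additional analyses {20b} and missing data {20c} name a stratum term or any other covariate.

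Two decisions rest on this model. The first is the test: "Differences will be considered statistically significant for the fixed effect of treatment groups if" p < 0.05. The second is clinical relevance: "The 95% confidence interval of the fixed effect size will be used to assess whether treatment difference reaches the minimally clinical important difference".

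**The concern.** Small blocks within strata keep the arms nearly equal within each defect-size class. Chance imbalance on defect size therefore contributes almost nothing to the true sampling variance of the treatment difference. A model without the stratum does not know this. It leaves the between-stratum differences in the between-patient variance and reports a standard error as if the imbalance could have occurred.

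If defect size is related to KOOS, the reported standard error is then larger than the real one, the confidence interval is wider than the design warrants, and the test rejects less often than its nominal 5%. The interval width matters in its own right here, because the interval is to be compared with the minimally clinical important difference. In a trial of 60 patients this is precision that can be had at almost no cost.

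**Working it through.** **1. The plan's own figure.** Sample size {14} gives "Based on a standard deviation of 15 [23], correlation of the repeated measures of 0.7", a "minimal clinical relevant treatment effect of 10 for KOOS", and "with a power of 0.8 and alpha of 0.05, a minimum of 44 patients should be included", "based on the Hotelling-Lawley trace".

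- Hotelling-Lawley, group by time, two arms, four visits (0, 3, 6, 9 months), equal correlations, arm differences (0, 10, 10, 10). The squared deviations of these differences from their mean of 7.5 sum to 56.25 + 3 × 6.25 = 75. The contrast variance is 225 × (1 − 0.7) = 67.5. The noncentrality at N = 44 is (44/4) × 75/67.5 = 12.2 on 3 and 40 df, which gives power 0.807.
- Cross-check on the change score: SD = 15 × √(2 × 0.3) = 11.62, and n per arm = 2 × (1.96 + 0.842)² × 135/100 = 21.2, so 22 per arm and 44 in total.

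The stated 44 reproduces. It makes no use of the stratification, so this point does not affect it.

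**2. Formula for the excess.** Let R² be the share of the variance of a patient's mean KOOS that the stratum explains. Then

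SE without stratum / SE with stratum = 1/√(1 − R²)

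actual two-sided type I error = 2 × [1 − Φ(1.96/√(1 − R²))]

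**3. From stratum difference to R².** The article gives no relation between defect size and KOOS, so a range of stratum differences g is assumed, with 40% of patients in one stratum (also assumed). The variance of a patient's mean over three post-baseline visits is 225 × (0.7 + 0.3/3) = 180. The variance due to the stratum is 0.4 × 0.6 × g² = 0.24g². So R² = 0.24g²/180.

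| Stratum difference g (KOOS points) | R² | SE ratio | Type I error |
|---|---|---|---|
| 0 | 0 | 1.000 | 0.050 |
| 3 | 0.012 | 1.006 | 0.049 |
| 5 | 0.033 | 1.017 | 0.046 |
| 10 | 0.133 | 1.074 | 0.035 |

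**4. Simulation check.** Stratified blocks of two and four, N = 60, patient means of three post-baseline visits analysed with and without the stratum, 6,000 runs per setting. Type I error is simulated with no treatment effect, power with a 10-point effect.

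| g | SE without | SE with | Excess | Type I error without | Power without | Power with |
|---|---|---|---|---|---|---|
| 0 | 3.44 | 3.45 | none | 0.050 | 0.808 | 0.807 |
| 3 | 3.45 | 3.43 | 0.6% | 0.047 | 0.822 | 0.824 |
| 5 | 3.44 | 3.39 | 1.7% | 0.046 | 0.812 | 0.821 |
| 10 | 3.46 | 3.21 | 7.5% | 0.035 | 0.820 | 0.858 |

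Simulation and formula agree. At g = 10 the half-width of the 95% interval is about 2.00 × 3.46 = 6.9 points without the stratum and 2.00 × 3.21 = 6.4 with it, roughly half a KOOS point wider. At g = 5 the difference is about 2.00 × (3.44 − 3.39) = 0.1 points.

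**5. How large R² could be.** Inverting the formula, g = √(180R²/0.24). R² of 5%, 10% and 20% would need stratum differences of about 6.1, 8.7 and 12.2 points. The last exceeds the 10-point treatment effect that the trial is sized to detect.

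**The case against.** **An unseen plan may add the term.** The article gives the model in one sentence, without random effects or covariance structure, and does not call it unadjusted. Covariates are often left to an analysis plan. That is fair as far as it goes, but this text is not silent: it lists the fixed factors and leaves out the variable that the randomisation was built on. A plan that adds the stratum would depart from the published list.

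**The effect depends on the contrast.** Baseline is a level of assessment date, and the sample size reproduces as a change-from-baseline test. A stratum effect that is constant over time cancels from such a contrast: with a 10-point stratum difference, its simulated standard error was 2.44 with or without the stratum. This stands and limits the point. The term that {20a} names for the test, however, is the group effect, and there the overstatement does arise.

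**Defect size may not be prognostic.** This also stands. A reader might infer that the reported standard error is certainly too large, but the article gives no association between defect size and KOOS, and without one there is no excess. Stratifying on it suggests that the sponsor thought it worth balancing, which is not evidence of its strength.

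**The benefit of stratifying is not lost.** A reader might also infer that it is wasted. It is not: the arms stay balanced and the estimate keeps its smaller true variance. Only the reported precision fails to take credit. Simulated power without the stratum remains above 0.80 at N = 60.

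**Conclusion.** The point holds as a modest and conditional loss of reported precision. The listed model omits the stratification factor and, to the extent that defect size predicts KOOS, overstates the standard error of the tested group effect. With SD 15, correlation 0.7 and an assumed 40/60 split, the excess is about 0 to 2% for stratum differences up to 5 points and about 7% at 10 points. The type I error is then about 0.046 and 0.035, and the power lost in simulation about 1 and 4 percentage points.

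A larger penalty, such as a standard error about 12% too large at R² = 20%, is not a reasonable headline, because it needs a stratum difference of about 12 points. Nor does the omission threaten validity: it introduces no bias, and the error is on the conservative side. The change is worth making because it is nearly free, not because the primary result would otherwise be unsound.

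**What to change.** Add the randomisation stratum (defect size < 4 or ≥ 4 cm², as entered at randomisation) as a fixed factor in the KOOS mixed model and in the other between-arm models. If the tested contrast is the change from baseline, add a stratum-by-visit term as well, since the main effect alone leaves that contrast unchanged.

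The cost is one degree of freedom, or a few more with the interaction. No new data are needed, because the variable is already recorded at randomisation. If defect size proves uninformative, almost nothing is lost (simulated SE 3.45 against 3.44). Fixing the term in advance also removes any later choice between adjusted and unadjusted results in an open-label trial.

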### Objectives {7}

The current phase III randomized controlled trial explores the efficacy of IMPACT compared to nonsurgical care in 60 patients with large (2–8 cm^2^) articular cartilage defects of the knee. We allow patients in the nonsurgical group to cross-over to the IMPACT group after 9 months of nonsurgical care. Follow-up will be at least 18 months after IMPACT. The primary objective is to compare the Knee Injury and Osteoarthritis Outcome Score (KOOS) at 3, 6, and 9 months follow-up. The secondary objective of this study is to examine morphology and proteoglycan content of repair tissue 6 and 18 months after treatment. Safety endpoints will be determined by the number of (treatment-related) adverse events. In addition, the incremental cost-effectiveness ratio (ICER) of IMPACT vs. nonsurgical care and vs. delayed surgical intervention will be calculated. More specifically, the effect of IMPACT compared with nonsurgical care and delayed surgical intervention in terms of healthcare resource use, productivity losses, and accompanying costs during the study period will be determined and extrapolated to a 5-year time horizon.

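### The primary test averages a pre-treatment baseline visit into the group effect, which shrinks a 10-point KOOS benefit to an expected 7.5 and cuts power to 58% at 60 patients

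*Protocol article*

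**What the plan says.** Section {20a} of the protocol article describes the primary analysis as a mixed model "with treatment group and assessment date of the PROMs (e.g., baseline, 3 months, 6 months) as fixed factors". Baseline is thus named as a level of the visit factor. The decision rule follows: "Differences will be considered statistically significant for the fixed effect of treatment groups if" p is below 0.05. The same coefficient then carries the judgement of clinical relevance: "The 95% confidence interval of the fixed effect size will be used to assess whether treatment difference reaches the minimally clinical important difference". The section mentions neither a group-by-visit term nor a baseline covariate.

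Two other sections describe a different quantity. Objectives {7} states: "The primary objective is to compare the Knee Injury and Osteoarthritis Outcome Score (KOOS) at 3, 6, and 9 months follow-up". Sample size {14} plans for the "treatment effect up to 9 months postoperatively) based on the Hotelling-Lawley trace" and concludes that "a minimum of 44 patients should be included to detect a minimal clinical relevant treatment effect of 10 for KOOS"; this is then rounded up to 60.

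**The concern.** In a model with group and visit as fixed factors, the group coefficient is a single difference averaged over every visit in the outcome. If baseline is one of those visits, a difference that randomisation sets at 0 in expectation is averaged with the differences after treatment. Three things follow.

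- The estimate is pulled towards zero, and power falls against the effect the trial was sized for.
- A diluted coefficient is compared with an undiluted 10-point threshold. A larger trial would not cure this.
- Chance baseline imbalance enters the estimate directly instead of being adjusted out. With about 30 patients per arm and stratification on defect size only (Sequence generation {16a}), such imbalance is likely to be more than trivial.

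An additive model also imposes the same difference at all visits. That is implausible here: under Intervention description {11a}, full weight-bearing comes at 8 to 12 weeks and return to low-impact sport after 9 months.

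**Working it through.** **Inputs.** From Sample size {14}: "Based on a standard deviation of 15 [23], correlation of the repeated measures of 0.7", "with a power of 0.8 and alpha of 0.05", effect 10 points, minimum N = 44, final N = 60. Allocation is 1:1 (Trial design {8}). Visits: baseline, 3, 6 and 9 months. Assumed here, because the article does not say: equal correlation between all pairs of visits, complete data, and two-sided alpha.

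**The plan's own figure.** Take true group differences of 0, 10, 10, 10 and a Hotelling-Lawley test of group by time, with baseline as the first measure. The noncentrality is (N/4) × m′S⁻¹m, where m holds the differences between successive visits and S is their covariance. At N = 44 this is 12.22; with 3 and 40 degrees of freedom the power is 0.807. At N = 42 it is 0.784. So 44 is reproduced as a group-by-time test.

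A group main effect does not give 44 under a two-sided test:

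| Two-sided group main effect | N for 80% power |
|---|---|
| 3 follow-up visits, all differing by 10 | 60 |
| 4 visits, all differing by 10 | 58 |
| 4 visits, differing by 0, 10, 10, 10 | 100 |

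Two other routes also reach 44, both by normal approximation: a change score at one visit (46 with the t distribution), and a one-sided main effect with a 10-point difference at all four visits, baseline included.

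**The test as written.**

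- Expected coefficient: (0 + 10 + 10 + 10)/4 = 7.5.
- Variance of a patient's four-visit mean: 225 × (1 + 3 × 0.7)/4 = 174.4.
- SE = √(4 × 174.4/N): 3.98 at N = 44 and 3.41 at N = 60.
- Power (noncentral t): 0.453 at N = 44 and 0.581 at N = 60.
- Typical 95% interval at N = 60: about 7.5 ± 6.8.
- True follow-up difference needed for the coefficient to equal 10: 10/0.75 = 13.3.

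A simulation of 200 trials with the additive random-intercept model at N = 60 gave a mean estimate of 7.6 and power of 0.63, in line with these values within simulation error.

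**Alternatives, true difference 10 at each follow-up visit.**

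| Tested quantity | Variance | Power, N = 44 | Power, N = 60 |
|---|---|---|---|
| As written (4 visits, baseline included) | 174.4 | 0.45 | 0.58 |
| Mean of 3 follow-up visits, unadjusted | 225 × 0.8 = 180 | 0.68 | 0.81 |
| Mean of 3 follow-up visits minus baseline | 225 × 0.4 = 90 | 0.93 | 0.98 |
| Mean of 3 follow-up visits, baseline-adjusted | 225 × (0.8 − 0.49) = 69.75 | 0.97 | 0.995 |
| 9 months only, baseline-adjusted | 225 × 0.51 = 114.75 | 0.86 | 0.94 |

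**Sensitivity.**

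- *Correlation.* For 0.3, 0.5, 0.7 and 0.8, power as written at N = 60 is 0.79, 0.67, 0.58 and 0.54.
- *Correlation decaying with time* (first-order autoregressive, 0.7 between adjacent visits; assumed). Baseline gets 38% of the weight and the expected coefficient is 6.2.
- *20% of each arm lost after 3 months* (assumed). The expected coefficient is 7.0.
- *Benefit that builds up* (0, 0, 5, 10). The coefficient as written is 3.75; the mean over the three follow-up visits is 5.

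**The case against.** The strongest reply is that the section does not say group and visit are the *only* terms, and that model detail may sit in a full protocol or SAP not shown here. The visit list opens with an e.g. and omits 9 months, so it is illustrative. Because 44 matches a group-by-time test, the authors may have meant to compare change from baseline and worded the tested effect loosely. This softens any claim about intent, but it does not rescue the text. Baseline is named explicitly, and so are the tested effect and the use of its interval. Adding an interaction would not help either: a group main effect averaged over visits would still include baseline. If the intended test is the one in Sample size {14}, the two sections contradict each other.

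Several points about size do stand. Not all of the gain comes from removing the dilution: at N = 60, dropping baseline takes power from 0.58 to 0.81, and the rest comes from baseline adjustment. A true 10-point benefit is more likely missed than found at 44 patients, but not at 60. The high power of the three-visit mean needs the full benefit by 3 months; under 0, 0, 5, 10 its adjusted power is 0.49 at N = 44 and 0.63 at N = 60. Finally, the dilution does not raise the type I error; it errs towards missing a benefit.

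**Conclusion.** The concern holds and should be corrected before analysis. Followed as written, the primary test targets three quarters of the mean follow-up difference, so a 10-point benefit has an expected estimate of 7.5 and the comparison with the 10-point threshold uses the wrong quantity. Power against the protocol's own target is 0.58 at 60 patients (0.54 to 0.79 for correlations of 0.8 down to 0.3) and 0.45 at 44, short of the planned 0.80.

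The one-quarter figure rests on four equally weighted visits, equal correlations and complete data. With only the three visits listed in the text it would be one third. The zero difference at baseline is an expectation under randomisation; Participant timeline {13} lists baseline questionnaires after randomisation in an open-label trial, so known allocation could affect those answers. The sample size of 44 is reproducible and is not itself the error.

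**What to change.** Rewrite the primary-analysis paragraph in {20a} along these lines: total KOOS at 3, 6 and 9 months is analysed in a mixed model with group, visit, group by visit, and baseline KOOS as a covariate (or in a model that constrains the groups to a common baseline mean). The primary estimate is the group difference averaged over 3, 6 and 9 months, with its 95% confidence interval; this estimate is tested at 0.05 and compared with 10 points.

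The three-visit mean fits Objectives {7} best. If the sponsor expects the benefit to build up slowly, the 9-month difference from the same model is the alternative, but one of the two must be fixed as primary in advance. Sample size {14} should then refer to the test chosen. Baseline questionnaires should be completed before allocation is revealed where that is still possible.

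The analysis change costs one paragraph of text, with no added patients, visits or measurements.

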### Interim analyses {21b}

There are no interim analyses planned.

### Methods for additional analyses (e.g., subgroup analyses) {20b}

There are no subgroup analyses planned.

### Methods in analysis to handle protocol non-adherence and any statistical methods to handle missing data {20c}

The primary outcome will be assessed using an intention-to-treat analysis. Missing data will be reduced to a minimum by using the appropriate measures described above. Mixed models do not require imputations for missing data. If any statistical method is needed to account for missing data in the secondary outcomes, multiple imputation will be used.

### Plans to give access to the full protocol, participant-level data, and statistical code {31c}

The datasets used and/or analyzed during the current study can be made available by the corresponding author upon reasonable request and in agreement with the research collaboration and data transfer guidelines of the UMC Utrecht.

